### Oversight and monitoring

The Coordinating Centre manages the operational and logistical aspects, ensuring smooth trial execution, and the overall trial implementation. Protocol evaluation and amendments will be discussed at regular Coordinating Centre trial conduct meetings.

The roles outlined here may be performed by more than one person. i.e., the Project Manager may also do the role of the Data Manager. The roles include:

Principal Investigator (PI): Provides scientific leadership and oversees the entire trial. Ensures the trial adheres to regulatory requirements, supervises data analysis, and maintains overall responsibility for the study’s conduct.Project Manager: Manages day-to-day operations of the trial. Coordinates activities across sites, manages timelines and budgets, and oversees staff at the coordinating center.Data Manager: Handles data collection, management, and analysis. Ensures data quality, integrity, and compliance with data protection regulations. Manages databases and performs statistical analyses.Clinical Research Coordinators: This role supports the PI and Project Manager in trial implementation. They are based on-site in a clinical setting and are responsible for the handling patient recruitment, informed consent, data entry, and follow-up activities.Regulatory Affairs Specialist: Ensures compliance with regulatory requirements. Manages submissions to ethics committees and regulatory bodies and maintains regulatory documentation.Quality Assurance (QA) Officer: Monitors trial conduct to ensure compliance with protocols and regulations. Conducts audits, manages deviations, and implements corrective actions.Statisticians: Provide statistical expertise for study design and analysis. Develop statistical analysis plans, perform interim and final analyses, and assist with interpretation of results.Administrative Staff: Provide administrative support to the coordinating center team. Handle documentation, scheduling, and communication tasks.

The Trial Steering Committee (TSC) provides independent oversight of the clinical trial. It ensures the trial is conducted according to the protocol and addresses any issues that arise during the study. The TSC provides independent oversight, ensuring scientific integrity, regulatory compliance, and participant safety. The TSC will have oversight of the interim analyses and key decisions such as a stop-early decision. Trial conduct will be discussed at TSC meetings and on demand by local ethics committees. The TSC will include:

Independent Chairperson: Leads the TSC meetings and ensures unbiased oversight. Facilitates discussions, ensures all viewpoints are considered, and guides decision-making processes.Principal Investigator: Provides insights on trial progress and scientific aspects. Updates the TSC on trial status, protocol adherence, and emerging results.Independent Clinicians: Offer clinical expertise and independent perspectives. Review safety data, assess clinical implications, and provide recommendations based on their expertise.Regulatory Affairs Specialist: Ensures regulatory compliance and addresses regulatory issues. Provides updates on regulatory submissions, compliance, and any regulatory changes affecting the trial.

#### Decision rules.

Stopping for Safety: Predefined criteria for stopping the trial if a significant safety concern are identified; for instance, if the incidence of severe adverse events is above what is expected.Stopping for Efficacy: Criteria for stopping the trial early if rectal swabs show clear and overwhelming evidence of inferiority, based on predefined statistical thresholds and thus it is futile to continue. A cutoff of 0.35 difference in accuracy for inferiority with an alpha of 0.05 at interim analyses will be used to support decisions on continuing, modifying, or stopping the trial. As this is a diagnostic test trial, the decision to stop the trial must be multifactorial in nature and made by the Trial Steering Committee.

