### Sample size calculation

A sample size analysis with a wide range of input parameters, as described by Hajian-Tilaki 2014, demonstrates that less than 600 samples will be sufficient to cover a range of diseases (Fig 2) [16]. Assuming that 30% of samples will contain an organism (“proportion positive”) with an expected sensitivity of at least 95% (“sensitivity priors”) means we will require a sample size of no more than 61 paired samples. As the prevalence of disease in samples decreases, the sample size required is higher. For a sensitivity of 95% and a prevalence of 20%, the sample size increases from 61 to 92. These estimates are based on general sensitivity assumptions and a simplified disease prevalence model, with the literature reporting non-specific prevalence to be approximately 25%, and sensitivity estimates typically >90% [17–20]. These estimates may change slightly as recruitment progresses and the distribution of pathogens becomes clearer. To address potential variability across different pathogens, stratified analyses will be conducted. Power calculations for key pathogen subgroups indicate that, for a sensitivity of 95% (with a range of 90–99%), a minimum of 73 positive samples is required per pathogen subgroup.

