#### Interim analysis.

Interim analyses will be part of a yearly steering committee meeting or at every 100 participants recruited, whichever comes first. The trial will implement a modified alpha spending function to guide decisions on early stopping. Initially, at 100 participants, a non-inferiority margin of 0.35 will be applied. This threshold will decrease by 0.05 at each subsequent interim analysis, reaching a final margin of 0.10 after 500 participants have been recruited. If the observed difference exceeds the non-inferiority margin at an interim analysis, the trial will be stopped for inferiority.

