#### Objectives of interim analysis.

Recruitment Rates: Assess the rate of recruitment and discuss the barriers and facilitators to successful participant recruitment.Safety Monitoring: Ensure participant safety by identifying any significant adverse events early. Review adverse event reports, including severity, relatedness, and unexpected events. Analyse differences in safety profiles between the rectal swab and bulk faeces groups.Efficacy Assessment: Non-inferiority assessments will be performed to monitor for inferiority of rectal swab PCR in comparison with traditional bulk faeces testing. Evaluate the primary endpoint of difference of accuracy of specimen collection methods, the rate of pathogen detection.Trial Continuation Decision: Provide data to support decisions on continuing, modifying, or stopping the trial.Compliance and Protocol Adherence: Assess the adherence to study protocols, including the proper collection and handling of specimens.

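### The fixed 0.35 interim cutoff is set on overall accuracy, where even a swab that detects nothing loses only 0.20 to 0.30 at the planned positivity; the declining margins would catch such a swab, but late

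*Protocol article*

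**What the plan says.** Two sections of the protocol article give a numerical interim rule, and a third names what is measured.

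- **Decision rules:** "A cutoff of 0.35 difference in accuracy for inferiority with an alpha of 0.05 at interim analyses will be used". This is one fixed cutoff, offered as support for a multifactorial decision by the Trial Steering Committee.
- **Interim analysis:** "Initially, at 100 participants, a non-inferiority margin of 0.35 will be applied", and then "This threshold will decrease by 0.05 at each subsequent interim analysis, reaching a final margin of 0.10 after 500 participants have been recruited". The consequence is firm: "If the observed difference exceeds the non-inferiority margin at an interim analysis, the trial will be stopped for inferiority". This section does not name the scale of the difference.
- **Objectives of interim analysis:** "Evaluate the primary endpoint of difference of accuracy of specimen collection methods, the rate of pathogen detection".

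The Outcomes section lists accuracy as a measure separate from sensitivity, and the Primary outcomes section makes bulk faeces PCR the gold standard. The Sample size calculation section supplies the positivity: "Assuming that 30% of samples will contain an organism", a lower case ("For a sensitivity of 95% and a prevalence of 20%, the sample size increases from 61 to 92"), and a literature figure ("with the literature reporting non-specific prevalence to be approximately 25" per cent). It expects a sensitivity of 95% or more.

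**The concern.** The trial asks whether the swab finds the organism when bulk faeces PCR does. Overall accuracy pools that question with agreement on negatives, and at 20 to 30% positivity the negatives make up 70 to 80% of pairs. A swab can therefore miss most or all infections and still show a modest accuracy difference. If the margin lies above the largest loss that missed infections can produce, the rule cannot do its stated job of halting the trial when the swab is plainly inferior. Recruitment would continue, and the committee would receive a reassuring figure from an uninformative statistic.

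**Working it through.** **Inputs.** Positivity 20, 25 and 30%, expected sensitivity at least 95% (Sample size calculation). Fixed cutoff 0.35 with alpha 0.05, sidedness not stated (Decision rules). Margins starting at 0.35 and falling by 0.05 per look (Interim analysis). Accrual of 3 to 6 swabs per week for two years (Timeline).

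**Check of the plan's own figures.** With n = 1.96² × Se(1 − Se) / (d² × prev) and Se = 0.95, a half-width of d = 0.10 gives 60.8, so 61, at 30% positivity and 91.2, so 92, at 20%. With d = 0.05, 73.0 positives are needed, matching the stated 73 per pathogen subgroup. The half-widths are not stated and were back-solved. The positivity inputs are thus the ones the plan used. It states no operating characteristic for the interim rule, so there is none to reproduce.

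**What the difference measures.** With the reference accuracy equal to 1:

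difference = prev × (1 − Se) + (1 − prev) × (1 − Sp)

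For Se = 0 and Sp = 1 this equals the positivity: 0.20, 0.25 or 0.30. With Sp = 0.95 it is 0.24, 0.29 or 0.335, still under 0.35. If the measure is instead the difference in detection rate, it is prev × (1 − Se) − (1 − prev) × (1 − Sp). Its ceiling is again the positivity, and false positives then offset misses.

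**Fixed 0.35 cutoff, swab with Se = 0 and Sp = 1.** Exact binomial at 100 participants; 200,000 simulated trials for six looks, one per 100 participants:

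| Positivity | P(observed difference > 0.35) at 100 | Cumulative, six looks |
|---|---|---|
| 20% | 0.0001 | 0.000 |
| 25% | 0.009 | 0.010 |
| 30% | 0.116 | 0.145 |

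If a one-sided 95% lower bound must exceed 0.35, the cumulative figure is at most 0.003.

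**Declining margins, same swab, cumulative stopping probability.** Margins 0.35, 0.30, 0.25, 0.20, 0.15 and 0.10 at 100 to 600 participants, observed difference as trigger:

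| Positivity | 100 | 200 | 300 | 400 | 500 |
|---|---|---|---|---|---|
| 20% | 0.000 | 0.000 | 0.014 | 0.47 | 0.998 |
| 25% | 0.009 | 0.048 | 0.47 | 0.99 | 1.00 |
| 30% | 0.117 | 0.47 | 0.97 | 1.00 | 1.00 |

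With a one-sided 95% lower bound as trigger the stop comes later: 0.62 by 300 at 30% positivity, 0.77 by 400 at 25%, 0.88 by 500 at 20%.

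**Against accrual.** Two years at 3 per week is 3 × 104 = 312 participants; at 6 per week it is 624. At 312 and 20% positivity, the last look is at 300, where the cumulative chance of stopping is 1.4%.

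**Sensitivity corresponding to the 0.10 margin.** Se = 1 − [0.10 − (1 − prev)(1 − Sp)] / prev:

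| Sp | 20% positive | 25% positive | 30% positive |
|---|---|---|---|
| 1.00 | 50% | 60% | 67% |
| 0.98 | 58% | 66% | 71% |
| 0.95 | 70% | 75% | 78% |

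**Partly sensitive swabs at 25% positivity.** With Se = 50% and Sp = 1 the difference is 0.125. The swab is stopped with probability 4% by 500 (margin 0.15) and 97% by 600 (margin 0.10). With Se = 70% and Sp = 98% the difference is 0.09, and the swab passes the 0.10 look at 600 about 82% of the time.

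**The schedule itself.** Five looks at 100 to 500 in steps of 0.05 give 0.35 − 4 × 0.05 = 0.15 at 500. The margin reaches 0.10 only at a sixth look, at 600. If 0.10 were applied at 500, the Se = 50% swab would be stopped about 95% of the time by then. The sample size section says fewer than 600 samples suffice, so a look at 600 may not take place.

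**The case against.** The strongest reply is that the declining schedule works. A reader might infer from the fixed cutoff that no interim rule here can stop a useless swab. The document does not support that: the Interim analysis section stops such a swab with 97 to 99.8% probability at 300, 400 or 500 participants, depending on positivity. This stands, and it limits the charge to the fixed cutoff and to the early looks.

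A reader might also infer that a swab missing a third to a half of infections could be declared non-inferior at the end. The document does not say so. Exceeding the margin leads to stopping; nothing says that staying within it establishes non-inferiority. Sensitivity and positive agreement are primary outcomes reported with 95% confidence intervals, so a poor sensitivity would be visible.

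The rule is also meant to be coarse and advisory, and a committee that sees the 2×2 table would probably notice near-zero sensitivity. Patient results come from bulk faeces, so continuing mainly costs resources. This lowers the severity, but it does not make the statistic informative.

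Finally, the result depends on reading accuracy as overall accuracy and on the case mix. The first reading is well supported, because the Outcomes section lists accuracy beside sensitivity. On a sensitivity scale a useless swab would differ by 1.0 and the point would vanish, which is a reason to name the measure. Recruitment aimed at a high pre-test probability could push positivity above 35%, where the 0.35 cutoff can bind. The sensitivity the rule tolerates would then still move with case mix.

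**Conclusion.** The point holds for interim monitoring and should be fixed; it does not undermine the final analysis. At the plan's own positivity, the fixed 0.35 cutoff lies above the expected accuracy difference of a swab that detects nothing, and such a swab is stopped with probability at most 14.5% over six looks. The declining margins do catch it, but only at 300 to 500 participants. At the low end of stated accrual with 20% positivity, that point is not reached. The 0.10 margin corresponds to a sensitivity of 50 to 67% if specificity is perfect, or 58 to 78% if it is 0.95 to 0.98, against the planned 95% or more.

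Separately, the two sections conflict: fixed against declining margins, and a supporting role against a firm stop. The schedule also does not reach its stated end at 500 in the stated steps.

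The figures assume that accuracy means overall accuracy, that looks fall every 100 participants, that positivity is 20 to 30%, and, unless noted, that the observed difference is the trigger.

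**What to change.** In Interim analysis, Objectives of interim analysis and Decision rules, name the measure and set the inferiority margin on loss of positive agreement (1 − sensitivity) among bulk-positive pairs. Add a separate criterion on loss of negative agreement among bulk-negative pairs. Judge each with a confidence bound at the stated alpha, giving its sidedness, and keep overall accuracy as a descriptive figure. State one schedule of margins whose steps reach the intended final value at the intended number of participants, and say whether crossing it requires a stop or informs the committee.

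The change is to wording only. Both agreement measures are already primary outcomes, so no new data are needed.

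The price is precision: at 100 participants there are only 20 to 30 bulk-positive pairs. A useless swab would still be obvious. If all 20 are missed, the exact one-sided 95% lower bound on the miss rate is 0.05^(1/20) = 0.86. A swab missing half would be less clear: 0.50 − 1.645 × √(0.25/20) = 0.32, which would not exceed 0.35 if that value were kept. The margins therefore need to be chosen afresh for the new scale.

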### Adverse event reporting

An adverse event (AE) is any untoward medical occurrence in a patient or clinical trial participant administered a medicinal product and that does not necessarily have a causal relationship with this treatment. An adverse reaction is any untoward and unintended response to an investigational medicinal product related to any dose administered. Probable and/or definitely related AEs are defined as adverse reactions for this trial.

A serious adverse event (SAE)/serious adverse reaction (SAR) is any adverse event/adverse reaction that results in death, is life-threatening, requires hospitalisation or prolongation of existing hospitalisation, results in persistent or significant disability or incapacity.

AEs will be classified according to:

SeverityMild: Adverse events that are easily tolerated and do not interfere with daily activities. These could include minor discomfort or irritation at the site of the rectal swab.Moderate: Events that cause some interference with daily activities but are not dangerous. Examples may include moderate pain, cramping, or a temporary increase in bowel movement frequency.Severe: Events that significantly interfere with daily activities or pose a risk to health. Severe adverse events might involve intense pain, bleeding, or infection requiring medical intervention.ExpectednessExpected Adverse Events: These are events that are known to occur based on previous studies or the nature of the procedures. For rectal swabs, this could include expected mild discomfort or minor bleeding.Unexpected Adverse Events: Events that are not anticipated based on prior knowledge. Unexpected events could be severe allergic reactions, systemic infections, or unusual gastrointestinal symptoms.Relatedness to ProcedureDefinitely Related: There is a clear, direct link between the adverse event and the rectal swab procedure. An example is rectal bleeding immediately following the swab.Probably Related: There is a reasonable likelihood that the event is related to the procedure, but other factors could be involved. For instance, discomfort that occurs after the procedure and subsides soon afterward.Possibly Related: The event could be related to the procedure but could also be attributed to other causes. This might include abdominal pain occurring days after the procedure.Unrelated: The event has no apparent connection to the procedure. An example is an adverse event like a headache, which is likely due to other factors.4. Type of Adverse EventLocal Adverse Events: These are events occurring at the site of the rectal swab. They might include irritation, redness, or bleeding.Systemic Adverse Events: Events affecting the body beyond the local site, such as fever, nausea, or generalised infection.Procedure-Related Adverse Events: Specific to the process of specimen collection, like discomfort during the swab insertion or difficulties with the bulk faeces collection method.Non-Procedure-Related Adverse Events: Unrelated to the procedure itself, such as a common cold or unrelated illness occurring during the trial period.

### Dissemination plan

We will aim for a comprehensive local dissemination plan (including national conferences, local news networks, maximum reach for local population), progressing to international journals and conferences. Overall, this dissemination plan will reach consumers and the general public, clinicians, pathologists that may perform these tests and academics that may use this in their future work.

## Discussion

We will recruit participants through a streamlined referral process involving clinicians and local study coordinators. Initially, clinicians who encounter potential participants meeting the study criteria during routine medical visits will introduce the study to these patients. They will provide a brief overview of the study’s purpose, procedures, and potential benefits, and assess the patients’ interest in participating. If the patient expresses interest, the clinician will refer them to the study coordinator.

The study coordinator will then be responsible for the enrollment process. This will begin with contacting the referred patients to discuss the study in greater detail, answer any questions they may have, and obtain informed consent. Once consent is obtained, the coordinator will enroll the participant in the study and provide them with a rectal swab and bulk faeces testing kit. The coordinator will also give clear instructions on how to use the kits, ensuring the participant understands the procedures for collecting and sending samples. Throughout the study, the coordinator will remain available to support the participants, addressing any concerns and ensuring compliance with the study protocols. This systematic approach ensures thorough participant engagement and adherence to the study requirements. The study team staff will be focused on removing barriers for the participants. Firstly, making it easy for the swabs and faeces specimen containers to get to the participant (via overnight mail), and then ensuring ease of delivery of the specimens to the pathology laboratories or collection points.

The bulk faeces specimen and the rectal swab will be transported at 4°C and be retained for minimum one month as per standard laboratory protocols for such materials. A small sample (aliquot) of the bulk faeces specimen and the rectal swab will be retained for minimum one year after submission, or until the end of the project (whichever is later).

The bulk faeces test will be used to report positive or negative test results. For samples that are discordant (e.g., swab negative but bulk faeces positive for organism, or vice versa), results should be confirmed through additional testing according to internal laboratory protocol.

The trial process has been refined through consultation with the local Consumer Research Engagement Group (CREG). Continued engagement with the CREG throughout the lead-up to recruitment will help ensure that the study remains relevant, acceptable, and responsive to the needs and perspectives of the broader community.

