#### Control sample (bulk faeces).

The bulk faeces sample is used as the control sample in this study as this sample type is currently used in routine clinical practice. In this context, bulk faeces PCR testing is considered the gold standard. It is acknowledged that bulk faces PCR testing may be associated with technical or interoperability limitations. To minimise the uncertainty that this could pose on testing results, paired samples that do not produce the same results will be managed internally according to laboratory protocol.

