#### Minimum data requirements.

At a minimum, data collected for each participant should include:

Identifiers (name, address, date of birth, contact details, comorbidities)Recruitment details (date of recruitment, date of consent, proof of consent, date that test packs were posted, symptomatology, duration of symptoms, presence of blood in faeces (if applicable))Sample collection details (where samples were collected (e.g., at home), who collected the sample (e.g., self-collect), date and time each sample was collected, date samples were submitted to pathology lab)Bulk faeces and rectal swab test results (date that lab testing was conducted for each sample, presence of visible faeces for the rectal swab only, positive/negative detection results for each sample)Follow-up information (date of follow-up attempts, which sample was collected first as reported by the participant, rough estimate of time difference between samples collected, adverse event details, preferred sample method)

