#### Primary outcomes.

We will assess the sensitivity, specificity, positive and negative predictive value, and positive and negative agreement value, using 2x2 tables. The gold standard will be bulk faeces PCR testing. Sensitivity is the proportion of individuals with the disease who test positive with rectal swabs. We will assess the cycle threshold (CT) values using general linear models if the relationship is linear as expected and estimate the receiver operating curves and areas under the curve to assess for the potential to need differential CT value cutoffs. All results will be reported using 95% confidence intervals.

The R statistical suite will be used for all analyses and data visualisation. All estimates will be presented with 95% confidence intervals (CI). P-values <0.05 are deemed significant, and p-values <0.1 are considered trends.

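### Only discordant pairs are sent for confirmatory testing, and the plan does not say whether first-run or confirmed results fill the 2x2 tables; if confirmed results do, swab accuracy would be overstated

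*Protocol article*

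**What the plan says.** Four places in the protocol article bear on this.

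- **Discussion.** The trigger for further testing is disagreement in either direction: "For samples that are discordant (e.g., swab negative but bulk faeces positive for organism, or vice versa". For these pairs, "results should be confirmed through additional testing according to internal laboratory protocol". The sentence before reads "The bulk faeces test will be used to report positive or negative test results", without saying which run is meant.
- **Control sample (bulk faeces).** After conceding that bulk PCR has limitations as a reference, the section gives a purpose, "To minimise the uncertainty that this could pose on testing results", and a remedy: "paired samples that do not produce the same results will be managed internally according to laboratory protocol".
- **Statistical methods, Primary outcomes.** "The gold standard will be bulk faeces PCR testing". The measures are sensitivity, specificity, "positive and negative predictive value, and positive and negative agreement value, using 2x2 tables". Neither statement distinguishes a first-run from a confirmed result.
- **Minimum data requirements.** The result item is "positive/negative detection results for each sample". No separate item for a repeat result is listed.

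The article describes no confirmatory testing of pairs that agree.

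**The concern.** Repeating a test only where two methods disagree, and then analysing the repeat, is discrepant resolution. Errors shared by both specimens are left alone, while errors that show up as disagreement get a second chance to disappear. The decision to repeat the reference test also depends on the index test, so the resolved reference is no longer independent of the swab.

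The Introduction gives the aim as replacing bulk faeces testing with the swab. In that setting there is no bulk result to prompt a repeat, so the accuracy that matters is that of one unprompted swab run. A table filled with confirmed results would describe a different procedure, and one that favours the swab. If the interim comparisons used the same tables, the inferiority rule would also become harder to trigger.

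**Working it through.** **1. The plan's planning value.** The sample size section expects sensitivity of at least 95%. The usual precision formula is n = z² × Se(1 − Se) / (d² × prevalence), with z = 1.96 and Se = 0.95. The half-width d is not in the text, so it is inferred here.

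- d = 0.10, prevalence 30%: 60.8, so 61.
- d = 0.10, prevalence 20%: 91.2, so 92.
- d = 0.05, positives only: 72.99, so 73.

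All three stated figures reproduce. The sample size is not in dispute; 95% serves below only as the benchmark.

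**2. Direction if confirmed results are substituted.** Suppose one result of a discordant pair changes:

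| First run | Change on repeat | New cell | Effect |
|---|---|---|---|
| swab −, bulk + | swab becomes + | true positive | sensitivity up |
| swab −, bulk + | bulk becomes − | true negative | sensitivity and specificity up |
| swab +, bulk − | swab becomes − | true negative | specificity up |
| swab +, bulk − | bulk becomes + | true positive | sensitivity and specificity up |

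Pairs that agree are left as they are, so overall agreement rises or stays the same whatever the repeats show. In a search over 200,000 random tables agreement never fell. Sensitivity, specificity and both predictive values never fell either, provided that discordant pairs stayed put or became concordant.

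The exception is a double flip. If a swab-positive, bulk-negative pair becomes swab-negative, bulk-positive, it stays discordant and a false positive becomes a false negative. With 162 true positives and 18 misses, one such pair takes sensitivity from 162/180 = 90.0% to 162/181 = 89.5%.

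**3. Size for sensitivity (all inputs assumed).** First-run sensitivity is 90%, and a share r of misses converts.

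- Swab turns positive: Se = 1 − 0.10 × (1 − r). r = 0.30 gives 93%; r = 0.50 gives 95%.
- Bulk turns negative instead: Se = 0.90 / (0.90 + 0.10 × (1 − r)). r = 0.30 gives 0.90/0.97 = 92.8%; r = 0.50 gives 0.90/0.95 = 94.7%.

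For the number of pairs, take 500 participants (the last interim threshold) at about 25% prevalence (the literature figure in the sample size section): 500 × 0.25 = 125 positives. Misses are 125 × 0.10 = 12.5. Converted pairs are 12.5 × 0.30 = 3.75 and 12.5 × 0.50 = 6.25, so about 4 to 6.

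**4. Range.** Assumed: 30% positive, first-run specificity 97%, swab results converting, and the same r for both kinds of discordance. The discordant share is D = 0.30 × (1 − Se) + 0.70 × 0.03, and agreement afterwards is 1 − D × (1 − r). Cells show sensitivity / overall agreement, in percent.

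| First run | r = 10% | r = 25% | r = 50% | r = 75% |
|---|---|---|---|---|
| 85 / 93.4 | 86.5 / 94.1 | 88.8 / 95.1 | 92.5 / 96.7 | 96.3 / 98.4 |
| 90 / 94.9 | 91.0 / 95.4 | 92.5 / 96.2 | 95.0 / 97.5 | 97.5 / 98.7 |
| 95 / 96.4 | 95.5 / 96.8 | 96.3 / 97.3 | 97.5 / 98.2 | 98.8 / 99.1 |

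**5. A limiting case showing the mechanism.** Let swab and bulk each be positive in 30% of 600 pairs, independently: 54 true positives, 126 false positives, 126 misses, 294 true negatives. Sensitivity is 54/180 = 30% and agreement 348/600 = 58%. Now repeat the bulk test at random (30% positive) in discordant pairs only. True positives become 54 + 0.3 × 126 = 91.8, misses 0.3 × 126 = 37.8 and true negatives 294 + 0.7 × 126 = 382.2. Sensitivity is 91.8/129.6 = 71% and agreement 474/600 = 79%, although the swab carries no information. This is not a forecast for the trial.

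**The case against.** The strongest reply is that confirmatory testing by itself biases nothing. The harm needs substitution into the tables, and no sentence in the article says that this will happen. The Discussion sentence follows one about reporting bulk results, and the Timeline section returns those results to the patient, so the repeat could serve clinical reporting only. Which run of a repeated assay is analysed is often settled in an analysis plan or laboratory protocol, and neither is shown here.

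Much of this stands, and it rules out several stronger readings that a reader might infer:

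- *That the trial will analyse confirmed results.* The article is silent on this.
- *That the Control sample section prescribes re-testing.* It speaks only of internal management. Additional testing appears in the Discussion, which does not repeat the stated purpose.
- *That repeats of concordant pairs are ruled out.* The article provides none, which is not a prohibition.
- *That every accuracy measure must rise.* Only overall agreement is bound to rise or stay the same; a double flip can lower sensitivity.
- *That the data set can hold only one result per specimen.* The list is expressly a minimum.
- *That the size is known.* The discordance rate, the conversion rate and the 125 positives are not in the article.

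What does not stand is that this is merely an omitted detail. The article itself sets up a step triggered by disagreement. It offers the handling of such pairs as the answer to the reference test's limits, and hands that handling to the laboratory. Read together with the Primary outcomes section, this leaves a natural route for resolved results into the primary tables.

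**Conclusion.** The point holds in conditional form. The article prescribes confirmatory testing for discordant pairs, provides none for concordant pairs, links the handling of discordance to uncertainty in the test results, and leaves open which result fills the 2x2 tables. If confirmed results replace first-run results, overall agreement cannot fall, and sensitivity and specificity will generally rise, so the accuracy of a single routine swab run would be overstated. On assumed inputs, a first-run sensitivity of 90% would be reported as 93% to 95% at conversion rates of 30% to 50%, through about 4 to 6 pairs if there are 125 positives. At the upper end that reaches the planning value with no change in the test. If first-run results are analysed, there is no bias from this source.

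**What to change.** State the same rule in the Control sample, Primary outcomes and Discussion sections: the primary 2x2 tables use the first valid result of each swab and of each bulk specimen. Record re-test results of discordant pairs in separate fields. Report them only as a descriptive table (how many misses and extra swab positives were confirmed) or as a sensitivity analysis, never substituted into the primary estimates.

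The cost is a few sentences and the extra data fields; no additional testing is needed and the information from re-testing is kept. The downside is that the headline sensitivity may be a few points lower than a resolved figure.
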